#### **9.2.1 Study Reports**

In addition to the study-related documentation required by the regulatory authorities, three reports will be generated. The first interim report will be completed after the safety data from the Day 70 visits of Cohorts 1-6 have been compiled, for the purposes of deciding whether it is safe to proceed with enrollment into **Part II** of the study. The second interim report will be completed after the safety and primary immunogenicity data from the Day 140 visit of Cohorts 7-12 have been compiled and the study investigators have been unblinded. This report will serve as the basis for deciding whether to continue with future phase 1 testing of the vaccine (and which formulation) in children, which is presently being planned for Brazil in 2015.

A final report containing all safety and immunology data will be prepared after trial completion.

### **9.3 Retention of Records**

Trial-related documents will be maintained by the Investigator for a period of 2 years after final marketing approval of the vaccine, or if 2 years have elapsed since the formal discontinuation of clinical development of the product. The Sponsor is required to inform the Principal Investigator

as to when such documents need no longer be retained. Storage of all trial-related documents will be such that confidentiality will be strictly maintained.

#### **9.4 Protocol Revisions**

No revisions to this protocol will be permitted without documented approval from both the Sponsor and the IRBs that granted the original approval for the study. This does not apply to changes made to reduce discomfort or avert risk to study participants. Furthermore, in the event of a medical emergency, the investigators shall perform any medical procedures that are deemed medically appropriate. The Principal Investigator must notify the Sponsor of all such occurrences. Any change to the protocol will be submitted to the actively participating IRBs (GWUMC and CPqRR) as a protocol amendment, and changes not affecting risk to participants may be expedited, as appropriate.

#### **9.5 Clinical Investigator's Brochure**

Investigators will receive the current version of the Clinical Investigator's Brochure, which comprehensively describes all the available preclinical and human experience with the experimental vaccine. If relevant new information becomes available during the course of the trial, the investigators will receive the revised Investigator's Brochure.

#### **9.6 Study Monitoring**

The Sponsor (SVI or its designee) will monitor all aspects of the study, with respect to current Good Clinical Practices, and for compliance with applicable government regulations. Prior to the start of the study, the Principal Investigator will be informed of the frequency of monitoring visits and will be given reasonable notification prior to each visit. The objectives of a monitoring visit will be to verify the prompt reporting of SAEs, to check the availability of the signed Informed Consent for enrolled study participants, to compare CRFs and spreadsheets with source data for completeness and accuracy, to verify compliance with the clinical protocol, and to check investigational product accountability. During the monitoring visit, the Principal Investigator (and/or designee) and other study personnel should be available to discuss the study. Study documents must be available for review throughout the course of the study.

### **10 STATISTICAL CONSIDERATIONS**

#### **10.1 General Design**

The goal of this Phase 1 vaccine trial is to assess the safety, reactogenicity, and immunogenicity of *Na*-GST-1/Alhydrogel® and *Na*-GST-1/Alhydrogel®/GLA-AF in healthy adults compared to the Butang® hepatitis B vaccine. These parameters will be assessed in adults without any history of infection with or exposure to hookworm, as well as individuals previously infected with hookworm.

##### ***10.1.1 Description of the Statistical Methods to Be Employed***

The purpose of this trial is to estimate AE rates and patterns of immune response as well as to compare these rates and patterns between the investigational and comparator vaccines, in different doses of the *Na*-GST-1 formulations.

This section briefly describes the statistical methods to be used; a detailed analytical plan will fully describe the methods. The analytical plan will discuss the planned approaches to missing data. Deviations from the original analytical plan will be thoroughly documented and reported to the Sponsor.

Descriptive and hypothesis-testing approaches will be used to meet the protocol objectives as stated in **Section 2.0**. Estimates will be presented with their 95% confidence intervals. Formal statistical tests, as outlined below, will be used to compare doses. No formal adjustments for multiple comparisons will be made. Statistical tests will use a two-sided significance level of 5%.

**Primary Objective:** To estimate the frequency of vaccine-related AEs, graded by severity, for each dose and formulation of *Na*-GST-1.

AEs will be coded according to Medical Dictionary of Regulatory Activities (MedDRA™) preferred terms. The frequency, severity, and relationship of AEs for each vaccine formulation and dose cohort will be presented in tabular form using the MedDRA™ coded term and organized by MedDRA™ System, Organ, and Class (SOC) designations.

- The frequency of immediate, systemic, and local injection site AEs will be summarized by SOC and preferred term.
- A line listing of each clinical and laboratory AE classified as immediate (within the first 2 hours), systemic, and local will be displayed in tables stratified by vaccine allocation and dose cohort.
- AEs will be summarized by severity and relationship to vaccine formulation by individuals and dose of *Na*-GST-1.
- The frequency of vaccine-related SAEs will be tallied as well as summarized by body system, by vaccine formulation and dose cohort.

The proportion of participants with at least one injection site AE will be compared by vaccine formulation and by dose cohort. The incidence of AEs will be compared across cohorts and not within cohorts. Therefore, the data for all participants who receive the hepatitis B vaccine (8 in total) will be summarized and compared to those who receive 10 µg *Na*-GST-1/Alhydrogel® (n=10), to those who receive 10 µg *Na*-GST-1/Alhydrogel®/GLA-AF, and so on. By merging the AE data of all participants who receive the same vaccine (hepatitis B, *Na*-GST-1/Alhydrogel®, or *Na*-GST-1/Alhydrogel®/GLA-AF), even if the individuals are not in the same cohort, the strength of the comparisons will be increased.

Laboratory results (hematological and clinical chemistry) will be examined for trends over time and any clinically significant values for individuals will be reported.

Secondary Objective 1: To determine the dose that generates the highest anti-*Na*-GST-1 IgG antibody response at Day 126, as determined by an indirect enzyme-linked immunosorbent assay (ELISA).

- a. The proportion of participants with detectable anti-*Na*-GST-1 responses will be summarized as a descriptive measure.
- b. Geometric mean antibody responses will be compared between vaccine formulation and dose groups. Comparisons between groups will be made by a one-way analysis of variance (ANOVA) with pair-wise comparisons between dose cohorts made by contrasts. Data from participants receiving the same vaccine (e.g., hepatitis B, *Na*-GST-1/Alhydrogel®, or *Na*-GST-1/Alhydrogel®/GLA-AF) will be combined across cohorts to increase the strength of the comparisons.

Secondary Objective 2: To assess and compare the duration of antibody response to *Na*-GST-1.

- a. Immunogenicity responses will be summarized by vaccine formulation and dose of *Na*-GST-1, over time.
- b. Individual responses will be described over time and stratified by *Na*-GST-1 formulation and by dose of *Na*-GST-1.
- c. Antibody responses will be measured at Days 0, 14, 28, 56, 70, 84, 112, 126, 140, 200, 290, and 380. To exploit the multiple measures of antibody within each subject, a longitudinal model may be built (if possible) to describe the antibody response over time. The model will explore if there are any differences between *Na*-GST-1/Alhydrogel®, *Na*-GST-1/Alhydrogel®/GLA-AF and Butang®, and explore dose effects. As described for Secondary Objective 2, data from participants receiving the same vaccine will be combined across cohorts.

Secondary Objective 3: To perform exploratory studies of the cellular immune responses to the *Na*-GST-1 antigen both before and after immunization.

The following assays will be performed to assess the cellular immune responses to vaccination with *Na*-GST-1:

- a. Lymphocyte proliferative responses to *in vitro* stimulation with *Na*-GST-1.
- b. Cytokine and chemokine production *in vitro* in response to stimulation with *Na*-GST-1.
- c. Changes in *in vivo* PBMC subpopulations as determined by flow cytometry.

Summary statistics will be used to present these immunogenicity results. To assess the changes in lymphocyte proliferative responses over time, a generalized estimating equations model with robust standard errors will be constructed.

Should the study be terminated early (see **Section 8.5**), the investigative team will discuss with the SMC the reason for termination and determine which study questions can be addressed in an

unbiased manner with the available data. The available data will be analyzed and interpreted in light of early termination.

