## **2 OBJECTIVES**

### **2.1 Primary Objective**

1. To determine the frequency of vaccine-related AEs, graded by severity, for each dose and formulation of *Na*-GST-1.

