## **10.2 Sample Size**

This Phase 1 trial is not powered to detect statistically significant differences between groups. Even though comparative statistics for the safety variables will be computed, the study will have low power to detect anything other than very large differences in the incidence of local injection site and systemic side effects between the vaccination groups. This is done weighing the need to detect any possible untoward reactions against the need to limit the number of volunteers involved for safety purposes. The sample size of 102 for this study is within the range commonly used in Phase 1 trials for the initial assessment of the safety, tolerance and immunogenicity of an investigational vaccine. Incorporation of a comparator vaccine will enable broad initial estimates of the incidence of local injection site and systemic side effects and of immune responses among vaccine recipients.

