### ***11.3.3 Immunization with Na-GST-1/Alhydrogel® plus GLA-AF***

The possible local vaccine reactions to be expected are similar to those of Na-GST-1/Alhydrogel® administered without GLA-AF. However, in a study of another vaccine administered with GLA-SE (a formulation similar to GLA-AF), the frequency and intensity of local reactions were somewhat greater than when the vaccine was administered without GLA-SE.

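### No between-group AE comparison named in section 10.1.1 uses severity grade or injection number, so a graded comparison should be added beside the any/none proportion

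*Protocol*

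**What the plan says.** The primary objective (protocol section 2.1, restated in 10.1.1) concerns the frequency of vaccine-related AEs "graded by severity, for each dose and formulation of" Na-GST-1. Section 8.2.2, Table 4, grades pain, tenderness, erythema and induration/swelling at the injection site from 0 to 4. Section 7.5 gives every participant three injections.

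Section 10.1.1 tabulates and summarises AEs by severity, relationship, formulation and dose, and attaches 95% confidence intervals to estimates. It then names two between-group comparisons of AEs:

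- "The proportion of participants with at least one injection site AE will be compared by vaccine formulation and by dose cohort".
- A second comparison sets overall AE incidence in one cohort against another, without contrasting arms inside a cohort, and merges recipients of the same vaccine.

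Tests are two-sided at 5%, and "No formal adjustments for multiple comparisons will be made".

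On the adjuvant, section 11.3.3 reports that in a study of another vaccine given with GLA-SE "the frequency and intensity of local reactions were somewhat greater than when the vaccine was administered without GLA-SE". Section 1.11 allows for a minor rise in the incidence, the severity or both with MPL. Section 10.2 concedes that "the study will have low power to detect anything other than very large differences in the incidence of local injection site and systemic side effects".

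**The concern.** The injection-site comparison turns up to three injections, four signs and a five-level grade into one yes/no. A participant with a single episode of mild tenderness counts the same as one with Grade 3 pain after every dose. The objective is graded, and the protocol expects the adjuvant class to act on intensity as well as frequency, yet neither named comparison can register a shift in grade among people who react anyway.

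Pooling over signs and doses also raises the proportion with any event. If most Alhydrogel recipients have at least one mild reaction, little room is left for a difference to appear. The comparison could then show no difference when reactions with GLA-AF are more severe or recur more often. These data feed the interim report that informs which formulation goes on to children (section 9.2.1).

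**Working it through.** **Arm sizes.** Part I has 6 × 6 = 36 participants and Part II has 3 × 10 + 3 × 12 = 66, total 102, as stated. Alhydrogel alone: 3 × 6 + 3 × (8 + 2) = 48. With GLA-AF: 3 × 6 + 3 × 10 = 48. The formulation contrast is therefore 10 v 10 (one dose, Part II), 16 v 16 (one dose, both parts), 30 v 30 (Part II, all doses) or 48 v 48 (all).

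**The admitted low power is confirmed.** Section 1.10 gives local reactions in 7.6% to 16.7% of volunteers with aluminium-adsorbed vaccines. Reading these as per-injection rates with independent doses (an assumption), P(any) = 1 − (1 − p)³, which is 1 − 0.924³ = 0.21 or 1 − 0.833³ = 0.42. From those control rates, 80% power (normal approximation, two-sided 5%) needs a difference of about 27 to 29 points at 48 v 48, 35 at 30 v 30, 46 to 48 at 16 v 16, and 55 to 60 at 10 v 10.

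**Ceiling.** The protocol names no test, so Fisher's exact test is assumed. Set the GLA-AF arm at 100% and find how many Alhydrogel reactors still allow p ≤ 0.05.

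| Arms | Last significant | First not significant |
|---|---|---|
| 10 v 10 | 5/10 v 10/10, p=0.033 | 6/10 v 10/10, p=0.087 |
| 16 v 16 | 11/16 v 16/16, p=0.043 | 12/16 v 16/16, p=0.101 |
| 30 v 30 | 24/30 v 30/30, p=0.024 | 25/30 v 30/30, p=0.052 |
| 48 v 48 | 42/48 v 48/48, p=0.026 | 43/48 v 48/48, p=0.056 |

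The chance of 6 or more reactors among 10 is 0.25% if 16.7% is a per-participant rate, and 20% if it is per injection (P(any) = 0.42). It is 77% at an assumed 30% per injection (P(any) = 1 − 0.7³ = 0.66). At 16.7% per injection the limit is reached in 0.8% of 16-person arms and about 0.0005% of 30-person arms.

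**Power, model A** (3000 replicates). Assumptions: GLA odds ratio 3 for occurrence and 2 for severity; among control reactions 20% Grade 2 or higher and 4% Grade 3 or higher; participant random intercept SD 1.5. Any/none chi-square v Wilcoxon on summed grade:

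- 30 v 30, 16.7% per injection: 39% v 49%. With independent doses: 76% v 90%, a 14-point gain.
- 30 v 30, 30% per injection: 39% v 62%.
- 16 v 16, 30%: 24% v 35%. 10 v 10, 30%: 14% v 25%.
- At 7.6% the gain is about −1 to +6 points.
- If only frequency changes, the gain at 30 v 30 is 4 to 7 points at 16.7% and 10 to 19 at 30%.

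**Power, model B** (1500 replicates, standard error about 1.3 points). Assumptions: common odds ratio 2.5 across grade cut-points; 30% of control reactions Grade 2 or higher and 5% Grade 3; random intercept SD 1; 48 v 48.

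| Control rate per injection | Any/none chi-square | Worst grade | Summed grade |
|---|---|---|---|
| 7.6% | 47% | 46% | 48% |
| 16.7% | 58% | 62% | 66% |
| 30% | 56% | 67% | 78% |
| 50% | 44% | 66% | 83% |
| 70% | 21% | 67% | 84% |

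The gain depends on the score. At 30% per injection, worst grade adds about 11 points and summed grade about 22. With stronger within-person correlation (SD 2) the summed-grade gain is 5 points at 16.7%, 20 at 50% and 23 at 70%.

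**Intensity-only effect** (model B, 48 v 48, odds ratio 3 for Grade 2 or higher among reactors). Any/none chi-square rejects in 4% to 5% of trials at every rate tried, which is its type I error. Worst grade rejects in 6% at 16.7% per injection, 38% at 50% and 67% at 70%; summed grade in 6%, 20% and 49%.

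**The case against.** The strongest reply is that the primary objective is estimation ("To estimate the frequency of vaccine-related AEs, graded by severity, for each dose and formulation of" Na-GST-1) and that section 10.1.1 delivers it in graded form. A shift in intensity would appear in those tables even if one test missed it. No passage makes this p-value a decision rule, and grade already enters the suspension criteria (section 8.5). Low power is disclosed, and a graded test does not cure it: model A gives 25% at 10 v 10 and 35% at 16 v 16, both at an assumed 30% per injection. Section 10.1.1 also leaves detail to a separate analytical plan, which is not at hand.

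Most of this stands, and it rules out several stronger inferences. A reader might take the injection-site proportion to be the only safety comparison; AE incidence is compared too, though also without grade. A reader might infer that the analysis cannot see intensity; it can, descriptively. A reader might conclude that the protocol's own rates imply a severe power loss; they do not, and section 1.10 gives them per volunteer, so even compounding them over three doses is an assumption. The documents describe the expected adjuvant effect only as minor or somewhat greater, so the odds ratios of 2 to 3 are assumptions as well.

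The deferral to the analytical plan does not dispose of the point. The protocol itself fixes the any/none endpoint and says cohorts are merged to strengthen the comparisons. Disclosed low power is no reason to leave collected grades out of the comparison.

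**Conclusion.** The point holds as a weakness of the named comparisons. Neither uses grade or injection number, and the any/none test has no power beyond alpha for a pure intensity effect.

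For a combined effect at 7.6% to 16.7% per injection, the loss against a rank test on summed grades is about 0 to 14 points. With 30 or more per arm it exceeds about 15 to 20 points only at assumed rates of 30% or more, and not in every setting there. The gain from worst grade alone is smaller. These sizes rest on the assumed per-injection reading, odds ratios, grade split and within-person correlation. The Fisher limits rest only on the arm sizes and the choice of test.

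It would go too far to say that the primary objective fails or that the any/none proportion should be dropped. The trial stays estimation-based with low power, and a graded test improves sensitivity without making the trial confirmatory.

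**What to change.** Keep the any/none proportion, shown with its exact 95% CI, and add to the same paragraph of section 10.1.1:

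> The worst injection-site grade per participant (Table 4, 0-4) will also be compared by vaccine formulation and by dose with an exact Wilcoxon rank-sum test, with an effect estimate and 95% CI. The grade summed over the three injections will be compared in the same way as a sensitivity analysis. The proportion with Grade 2 or higher will be shown with an exact 95% CI.

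Worst grade comes first because a summed or averaged grade lets one Grade 3 reaction equal three Grade 1 reactions, and is distorted when a participant stops dosing early. The summed grade is retained because it uses all the injections and usually gained more power in the simulations.

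The cost is some wording and a few lines of code. No participants, visits or assessments are added. The downside is a further comparison without multiplicity adjustment and a less familiar summary.

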## 4 STUDY DESIGN

### 4.1 Overall Design

The study will be conducted in two parts (**Table 1**). **Part I** of the study will be an open-label dose-escalation phase 1 trial of *Na*-GST-1/Alhydrogel® administered with or without GLA-AF conducted in Belo Horizonte in healthy adult volunteers without history of hookworm infection. **Part II** will be a randomized, controlled, double-blind phase 1 dose-escalating clinical trial in healthy adult volunteers living in the hookworm-endemic area of Americaninhas. This part of the study is designed to evaluate the safety, reactogenicity, and immunogenicity of *Na*-GST-1/Alhydrogel® with or without GLA-AF, as compared to Butang® hepatitis B vaccine.

Safety parameters will be monitored throughout both parts of the study. The primary immunological endpoint for both parts will be the measurement of the antigen-specific antibody response.

Prior to beginning study-related activities in Americaninhas in Part II of the study, the consent and cooperation of representative community members will be sought, after which volunteers will be invited to participate in the study. In both Belo Horizonte and Americaninhas, after providing written informed consent and passing the informed consent comprehension questionnaire, volunteers will undergo eligibility screening, including a complete medical history, physical examination, hematology and coagulation testing, serum glucose testing, liver and renal function testing, HIV antibody testing, Hepatitis B and C serology, and urinalysis; urine pregnancy testing will be performed on all female volunteers. In addition, all volunteers will be tested for serum IgE antibodies to *Na*-GST-1, and a fecal examination will be performed for ova and parasites. All clinically significant abnormalities will be reviewed with volunteers and referral for follow-up care will be provided. After screening, those volunteers determined to be eligible, based on the inclusion and exclusion criteria described in **Section 5** in this protocol, will be invited to participate in the study.

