### 4.3 Group Allocation

Dose cohorts will be enrolled consecutively. In **Part I** of the study, within Cohort 1 all participants will receive the 10 µg dose of *Na*-GST-1/Alhydrogel®; within Cohort 2, all will receive 10 µg of *Na*-GST-1/Alhydrogel®/GLA-AF, and so on. In **Part II** of the study, within Cohorts 7, 9 and 11 of 10 participants, 8 will be randomly assigned to receive *Na*-GST-1/Alhydrogel® and 2 to receive Butang® (see **Section 7.3**). Within Cohort 7, Cohort 9, and Cohort 11, those randomized to receive *Na*-GST-1/Alhydrogel® will receive a dose containing 10 µg, 30 µg and 100 µg of *Na*-GST-1, respectively. Also in Part II of the study, within Cohorts 8, 10, and 12 of 12 participants, 2 will be randomly assigned to receive *Na*-GST-1/Alhydrogel® and 10 to receive *Na*-GST-1/Alhydrogel®/GLA-AF. Within Cohorts 8, Cohort 10, and Cohort 12, participants will receive a dose containing 10 µg, 30 µg and 100 µg of *Na*-GST-1, respectively.

In both **Part I** and **Part II** of the study, 1 or 2 additional eligible volunteers above the number to be enrolled in a given cohort may be scheduled for a Day 0 visit, if possible. On the day of first vaccination, the first volunteers who arrive at the study clinic will be evaluated for continued eligibility and vaccinated in the order that they arrive; the additional eligible volunteers will be kept as alternates if some of the first arrivals cannot be vaccinated on the day of first vaccination (i.e., due to pregnancy, withdrawal of consent, etc.). If the alternates are not vaccinated, they will be invited to participate as members of the next dose cohort. Those alternates for the final cohorts in both Part I and Part II who are not vaccinated and therefore not enrolled in the study, will be offered vaccination with a non-study, licensed vaccine such as the tetanus toxoid or influenza vaccine.

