17. Positive ELISA for HCV.
18. Positive ELISA for HBsAg.
19. Positive ELISA for HIV.
20. Use of corticosteroids (excluding topical or nasal) or immunosuppressive drugs within 30 days of starting this study.
21. Receipt of a live vaccine within past 4 weeks or a killed vaccine within past 2 weeks prior to entry into the study.
22. History of a surgical splenectomy.
23. Receipt of blood products within the past 6 months.
24. History of allergy to yeast.
25. Anti-*Na*-GST-1 IgE antibody level above 0.35 kUA/L by the ImmunoCAP method.
26. For Part I only: history of previous infection with hookworm; residence for more than 6 months in a hookworm-endemic area; or, positive for hookworm infection on screening microscopic fecal examination.
27. For Part II Cohorts #7, #9, and #11 only: previous receipt of a primary series of any hepatitis B vaccine.

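### Section 10.1.1 rules out within-cohort AE comparison, but Part II randomises only within cohorts, so its two randomised contrasts are not analysed as such

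*Protocol*

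**What the plan says.** Section 4.1 describes Part II in these terms: it "will be a randomized, controlled, double-blind phase 1 dose-escalating clinical trial in healthy adult volunteers". Section 4.3 places the randomisation inside each cohort. In Cohorts 7, 9 and 11, "8 will be randomly assigned to receive" Na-GST-1/Alhydrogel and the other 2 receive Butang. In Cohorts 8, 10 and 12, "2 will be randomly assigned to receive" Na-GST-1/Alhydrogel and the other 10 receive the GLA-AF formulation. Entry to a cohort is not randomised: "Dose cohorts will be enrolled consecutively", and alternates who are not used are invited into the next cohort.

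Eligibility is not the same in all six cohorts. Exclusion criterion 27 in Section 5.2, "previous receipt of a primary series of any hepatitis B vaccine", applies to Cohorts 7, 9 and 11 only.

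For the AE analysis, Section 10.1.1 sets the rule "The incidence of AEs will be compared across cohorts and not within cohorts". It then merges everyone who received the same vaccine, on the ground that "even if the individuals are not in the same cohort, the strength of the comparisons will be increased". No stratification or adjustment by cohort is mentioned. The same section plans formal tests at a two-sided 5% level.

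**The concern.** The protocol fixes this rule; it does not leave it open. An analysis plan that compared Alhydrogel with Butang, or GLA-AF with Alhydrogel, inside the cohorts where people were randomised between them would contradict it.

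The merged formulation comparison is largely a comparison of cohorts, and the cohorts differ by design in two ways. Exclusion 27 makes eligibility differ between odd and even cohorts. Knowledge also differs: Section 4.4 sets out which vaccines each cohort may receive. Everyone in an even cohort gets Na-GST-1, with or without GLA-AF, whereas someone in an odd cohort may have had Butang. Section 1.13.1 justifies the blinded comparator as a guard against bias in reporting AEs and judging their cause. That guard covers comparisons within a cohort, not between cohorts.

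The formulation comparison matters because Section 9.2.1 uses the second interim report to decide whether to continue into children and with which formulation.

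**Working it through.** **Inputs.** Allocation counts come from Sections 4.1 and 4.3 and Table 1. Part II has three odd cohorts (7, 9, 11) of 8 Alhydrogel + 2 Butang, and three even cohorts (8, 10, 12) of 2 Alhydrogel + 10 GLA-AF. Each odd/even pair shares one antigen dose.

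**The plan's own figure.** Section 10.1.1 gives n=10 for the merged 10 µg Alhydrogel group. From the design this is 8 (Cohort 7) + 2 (Cohort 8) = 10, which agrees. The same sentence counts 8 hepatitis B recipients, whereas the design gives 3 × 2 = 6. That is a separate slip, and the figure 6 is used below.

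**How much of a cohort difference enters each contrast.** Suppose no vaccine effect, an AE rate r in odd cohorts and r + d in even cohorts.

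- Merged Alhydrogel, one dose: (8r + 2(r + d))/10 = r + 0.2d. Over all doses: (24r + 6(r + d))/30 = r + 0.2d.
- GLA-AF: r + d. Butang: r.
- GLA-AF minus Alhydrogel: **0.8d**.
- Alhydrogel minus Butang: **0.2d**.
- GLA-AF minus Butang: d.
- Within any even cohort, GLA-AF minus Alhydrogel: (r + d) − (r + d) = 0. Within any odd cohort, Alhydrogel minus Butang: r − r = 0.

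**What this could do to a test.** The documents give no AE rates, so take r = 30% as an assumption and let d range. The table shows the chance of a false-positive result from a two-sided 5% Fisher test of merged GLA-AF v Alhydrogel, by full binomial enumeration.

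| d (points) | Spurious difference 0.8d (points) | All doses, 30 v 30 | One dose, 10 v 10 |
|---|---|---|---|
| 0 | 0 | 2.6% | 1.2% |
| 10 | 8 | 5.7% | 1.8% |
| 20 | 16 | 16.5% | 3.7% |
| 30 | 24 | 36.7% | 7.2% |
| 40 | 32 | 62.8% | 13.4% |

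A cohort-stratified exact test of GLA-AF v Alhydrogel (three strata of 10 v 2; 20,000 simulations) rejected in about 2.3% to 2.4% of cases at common AE rates of 0.3, 0.5 and 0.7.

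**What stratification costs.** With equal variance per person, the information in a contrast is 1/(1/n1 + 1/n2), summed over strata. The SE ratio is the square root of merged over stratified information.

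- GLA-AF v Alhydrogel, all doses: merged 1/(1/30 + 1/30) = 15; stratified 3/(1/10 + 1/2) = 5; SE ratio √(15/5) = 1.73.
- Alhydrogel v Butang, all doses: merged 1/(1/30 + 1/6) = 5.0; stratified 3/(1/8 + 1/2) = 4.8; SE ratio √(5.0/4.8) = 1.02.
- Alhydrogel v Butang, one dose: merged (10 v 6) 1/(1/10 + 1/6) = 3.75; one cohort (8 v 2) 1/(1/8 + 1/2) = 1.6; SE ratio √(3.75/1.6) = 1.53.

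For GLA-AF v Alhydrogel at assumed AE rates of 0.8 v 0.3, power is about 62% with the stratified exact test and about 99% with the merged comparison (normal approximation). At 0.9 v 0.3 it is about 85% and close to 100%. The merged figures are valid only if cohorts do not differ. One cohort alone is too small to test usefully: the smallest attainable two-sided Fisher p is 0.022 for 8 v 2 and 0.015 for 10 v 2. The three cohorts of a kind have to be combined by stratification.

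**The case against.** The trial is small, and Section 10.2 says openly that it is not powered for between-group differences. The primary objective is to estimate AE frequency for each dose and formulation, and those estimates need no within-cohort comparison. Merging gives real precision at a single dose, as the ratios of 1.53 and 1.73 show. Dose comparisons and GLA-AF v Butang share no cohort, so they can only be made across cohorts. All of this stands. It supports keeping the merged tables and comparisons. It does not support ruling out the randomised ones, and low power does not remove bias.

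A reader might also infer more than the documents support:

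- **That open-label Part I is merged in.** The stated n=10 is Part II only; adding the 6 from Cohort 1 would give 16.
- **That the even cohorts are in effect unblinded.** Section 4.4 blinds allocation within every Part II cohort and keeps vaccinators out of AE assessment. Only the set of possible vaccines is known. Section 8.2.3 also classes all injection-site reactions as definitely related, so for those such knowledge could affect reporting or grading but not attribution.
- **That the randomised data are thrown away.** Those participants stay in the merged groups, and Section 10.1.1 also tabulates AEs by formulation and dose cohort. What is lost is the contrast.
- **That odd and even cohorts are separated in time.** In Table 3, Cohorts 8 and 9 start in the same week, as do 10 and 11. Same-dose pairs are only one or two weeks apart at minimum spacing.
- **That merging gains almost nothing.** The 2% figure holds only for all-dose Alhydrogel v Butang.
- **That exclusion 27 must be extended to all six cohorts.** Stratification already removes that imbalance from both randomised contrasts. The documents also give no reason why earlier hepatitis B vaccination would change reactions to Na-GST-1.

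**Conclusion.** The point holds as a defect in one rule. Section 10.1.1 excludes the only two contrasts that Part II randomises, and replaces them with merged comparisons that carry 80% of any odd/even cohort difference into GLA-AF v Alhydrogel and 20% into Alhydrogel v Butang. These shares follow from the allocation counts. At a single dose, the Butang share also assumes a common rate across the three odd cohorts.

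The size of d is unknown, so the documents do not show that a bias exists or how large it would be. The false-positive rates rest on an assumed 30% base rate. The exposure is greatest in the all-dose formulation comparison and modest in single-dose tests. The AE frequencies reported for each dose and formulation remain valid descriptions of the people who received them. What is affected is how differences between formulations are read.

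**What to change.** In Section 10.1.1:

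1. Delete the closing clause of the sentence that rules out within-cohort comparison.
2. Add two cohort-stratified exact analyses, for example exact Mantel-Haenszel, named as the randomised comparisons: Alhydrogel v Butang in Cohorts 7, 9 and 11, and GLA-AF v Alhydrogel in Cohorts 8, 10 and 12.
3. Keep the merged dose and formulation comparisons, labelled as non-randomised between-cohort comparisons. State that dose comparisons and GLA-AF v Butang can only be made this way.

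This changes wording and adds two analyses. It needs no new data and no change to eligibility. The randomised GLA-AF v Alhydrogel result will be imprecise, with the SE 1.73 times that of the merged comparison, and it pools over dose, so it does not answer the question dose by dose. For that reason it should stand beside the merged comparison and not replace it. For all-dose Alhydrogel v Butang the loss is about 2% in SE. The hepatitis B count in the same paragraph should be reconciled with the design in the same edit.
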